### Sample size calculation

For the primary outcome HRQoL, obtained with the SF-12, a sample size of 350 patients is required. To obtain a clinically relevant difference between groups of 3 points in the SF-12 summary scores, after a median of 12 months follow-up, 175 patients per group are needed (assumed standard deviation = 10 points, α = 0.05, β = 0.20) [46, 57–59].

However, for the EQ5D-5L, an important component for the secondary outcome cost-effectiveness, a sample size of 1400 patients (700 patients per group) is needed. A difference of 0.03–0.07 points between groups after a mean follow-up of 12 months is considered clinically relevant [44, 60, 61]. The standard deviation in dialysis groups ranges from 0.1 to 0.22 [62, 63]. Assuming a common standard deviation of 0.20 and the lowest, still clinically relevant score, a total of 1400 patients (700 patients per group) will be sufficient to detect a difference of 0.03 points in the EQ5D-5L score between groups (α = 0.05, β = 0.20).

When approximately 10% loss to follow up is taken into account, a group of 800 home dialysis patients and a comparison group of 800 ICHD patients has to be included in order to have sufficient power to analyse both outcomes. Since the ratio between PD patients and home haemodialysis (HHD) patients in the Netherlands is expected to be 3:1 in future years, the home dialysis group will consist of 600 PD and 200 HHD patients.

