## Background

In the Netherlands, over 6200 patients with End Stage Renal Disease (ESRD) are dependent on dialysis, and over the past 15 years, the number of dialysis patients has increased by more than 20% [1–3]. The burden of dialysis is high and the health-related quality of life (HRQoL), which is presently considered to be the most important outcome parameter in dialysis patients, is much worse than that of healthy people [4]. As patient survival is poor, with a median five-year survival rate of only 45%, optimising HRQoL is of great importance for this growing group of patients [5, 6].

Besides its impact on HRQoL, dialysis is also an expensive treatment. In the Netherlands, the estimated costs are approximately 570 million euro per year (639 million US dollars) and are still increasing. [Personal communications, [name], National Institute for Public Health and the Environment, 2019] This makes dialysis by far the highest cost-consuming treatment in internal medicine, not only calculated per individual patient, but also if total treatment costs are taken into account [7].

Home dialysis has a potential positive effect on HRQoL because it offers flexibility to patients and greater freedom [8]. Moreover, home dialysis is possibly a more cost-effective therapy if less nursing staff is needed, when patients perform their treatment autonomously or with help of an informal caregiver. Despite these potential advantages, currently more than 80% of dialysis patients are treated with in-centre haemodialysis (ICHD). Furthermore, the percentage of patients treated with home dialysis is steadily decreasing in the Netherlands, from 32% in 2002 to 18% in 2018. This decline is mainly attributable to a reduction in the number of patients performing peritoneal dialysis (PD), the main home based therapy, with 1519 PD patients (30% of total dialysis patients) in 2002 versus 894 PD patients (14% of total dialysis patients) in 2018 [1].

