### (Early) termination

For each participating patient, the study ends on 20 December 2021. Early study termination occurs if the patient withdraws from the study or stops dialysis treatment. Reasons to stop dialysis include kidney transplantation, recovery of kidney function, the wish to stop dialysis, or death.

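### The 10% loss allowance behind 800 per group is hard to reconcile with the protocol's own survival figure and its list of reasons for leaving the study; the effect on EQ-5D-5L power is modest.

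*Protocol article*

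**What the plan says.** Under Sample size calculation, the protocol article derives two sizes. The SF-12 needs 175 per group. For the EQ-5D-5L, "a sample size of 1400 patients (700 patients per group) is needed". The EQ-5D-5L inputs are a difference at the low end of the relevant range ("A difference of 0.03–0.07 points between groups after a mean follow-up of 12 months is considered clinically relevant") and a standard deviation near the top of the cited range ("Assuming a common standard deviation of 0.20 and the lowest, still clinically relevant score"; "The standard deviation in dialysis groups ranges from 0.1 to 0.22"). The stated aim is "to detect a difference of 0.03 points in the EQ5D-5L score between groups (α = 0.05, β = 0.20").

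The allowance for loss follows: "When approximately 10% loss to follow up is taken into account, a group of 800 home dialysis patients" and 800 in-centre patients are to be enrolled, and this is said to give enough power for both outcomes.

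Two other places bear on that allowance. The Background calls survival poor, "with a median five-year survival rate of only 45" per cent. The section (Early) termination says "Early study termination occurs if the patient withdraws from the study or stops dialysis treatment", and lists transplantation, recovery of kidney function, the wish to stop, and death as reasons for stopping dialysis.

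**The concern.** The EQ-5D-5L calculation, not the SF-12 one, produces the total of 1600. Its margin is thin: 800 enrolled against 700 required. The protocol defines five ways to leave (death, transplantation, recovery, choosing to stop, withdrawal) and allows about 10% for loss without saying which of them the figure covers. Its own survival figure suggests that death alone could use up that allowance within the first year.

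If the allowance is too small, the power claimed for EQ-5D-5L is somewhat optimistic. A utility difference that fails to reach significance could then be read as firmer evidence of no difference than it is, and the study's results are to feed the cost-effectiveness model.

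**Working it through.** **Inputs.** From Sample size calculation: difference 0.03, SD 0.20, α 0.05, β 0.20, 700 required and 800 enrolled per group, loss about 10%. From Background: 45% survival at five years. Two-sided testing is assumed because it reproduces the stated sizes.

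**1. Reproduce the plan.** n per group = 2 × (1.96 + 0.8416)² × (SD/difference)².
- SF-12: 2 × 7.849 × (10/3)² = 174.4, so 175, as stated.
- EQ-5D-5L: 2 × 7.849 × (0.20/0.03)² = 697.7, so 698; the plan says 700.
- Allowing for 10% loss: 700/0.90 = 778, rounded up to 800.

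The arithmetic is sound. The question is the 10%.

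**2. Loss that 800 can absorb.** 1 − 700/800 = 12.5%.

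**3. First-year deaths implied by 45% at five years.** At a constant hazard (assumption), the yearly rate is −ln(0.45)/5 = 0.1597 and one-year survival is 0.45^(1/5) = 0.852. Deaths are 14.8%, leaving 800 × 0.852 = 682.

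Power = Φ(0.03/(0.20 × √(2/n)) − 1.96). At n = 682 this is 79.1%, against 80.1% at n = 700.

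**4. Sensitivity to the shape of the hazard.** Weibull curves through 45% at five years, deaths only:

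| Shape | Year-1 deaths | Left per group | Power | Other exits that bring the group to 700 |
|---|---|---|---|---|
| 0.8 (falling) | 19.8% | 642 | 76.6% | already below |
| 1.0 (constant) | 14.8% | 682 | 79.1% | already below |
| 1.1 | 12.7% | 698 | 80.0% | already just below |
| 1.2 | 10.9% | 713 | 80.8% | 1.8% |
| 1.3 (rising) | 9.4% | 725 | 81.5% | 3.4% |

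The last column is 1 − 700/(number left). A rising hazard removes the deaths-only shortfall, but 700 then survives only if very few patients leave for any other reason.

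**5. Total loss.** The protocol gives no one-year rates for transplantation, recovery, stopping or withdrawal, so total loss is set by assumption. The detectable difference is 2.8016 × 0.20 × √(2/n).

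| Assumed total loss | Left per group | Power for 0.03 | Difference detectable with 80% power |
|---|---|---|---|
| 10% (plan) | 720 | 81.2% | 0.0295 |
| 20% | 640 | 76.5% | 0.0313 |
| 25% | 600 | 73.8% | 0.0323 |
| 30% | 560 | 70.9% | 0.0335 |

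SF-12 power for 3 points at SD 10 stays above 99% even at 40% loss (480 per group).

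**6. Effect of baseline adjustment.** With baseline correlation ρ, the residual SD is 0.20 × √(1 − ρ²). At ρ = 0.5 (assumption) this is 0.1732, and power is 87.3% at 640 and 82.6% at 560 per group. At 560, power reaches 80% when 1 − ρ² = 560/697.7, that is ρ of about 0.44.

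**The case against.** The case for leaving the paragraph alone is substantial.

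- **No calculation is wrong.** Both sizes and the inflation reproduce. This stands: the dispute concerns an assumption.
- **The documented shortfall is trivial and conditional.** Deaths alone cost about one point of power. Even that needs a constant hazard, and it applies a general dialysis survival figure to a cohort that excludes a life expectancy under 3 months. This also stands for deaths alone. It does not rescue the 10% once the other exits are counted, because the eligibility rule covers only events expected within 3 months.
- **Leaving before month 12 is not the same as contributing nothing.** The target is expressed at a mean follow-up of 12 months. EQ-5D-5L is also collected at 3 and 6 months, and multilevel or GEE analysis with multiple imputation is planned. In the cost-effectiveness model, utilities are combined with survival and transplantation is a modelled state. This stands and softens the point. However, the stated power comes from a plain two-sample formula that takes no credit for repeated measures.
- **The inputs are already cautious.** An SD of 0.20 is near the top of the cited range, and 0.03 is the smallest relevant difference. This stands. A reader might note that SD 0.22 needs 844 per group, more than are enrolled, but choosing 0.20 from a range of 0.1 to 0.22 is not an error. At 0.16, about 447 per group suffice.

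A reader might also add a 10% loss on top of the 14.8% deaths and conclude that power is about 75% or lower. The protocol does not say whether the 10% includes deaths, so it does not support stacking the two as though that were the plan's own assumption.

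**Conclusion.** The 10% allowance is not supported by the protocol's own figures. The 800 per group tolerates 12.5% total loss; the survival figure implies roughly that much or more from deaths alone unless the hazard rises over time, and four further exits come on top. Under the simple comparison used for the sample size, EQ-5D-5L power is 79.1% counting deaths only at a constant hazard, and 76.5% to 70.9% at an assumed total loss of 20–30%.

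A reader might infer that the study is underpowered, or that EQ-5D-5L power is in fact 70–75%. The documents do not support either. They give no one-year mortality or transplantation rates, the hazard shape is an assumption, and the planned longitudinal analysis recovers part of the loss. The primary SF-12 comparison is unaffected. This is a minor-to-moderate correction: it concerns one component of a secondary outcome, though it is the component that sets the total of 1600.

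**What to change.** Revise the last paragraph of Sample size calculation in one of two ways, without enrolling more patients.

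1. Replace the 10% by an anticipated total 12-month attrition that explicitly includes death, transplantation, recovery, stopping dialysis and withdrawal. Restate the EQ-5D-5L power (76.5% to 70.9% for 0.03 at SD 0.20), or the difference detectable with 80% power (0.031–0.034), over 20–30% loss.
2. Base the power on the planned repeated-measures model adjusted for baseline EQ-5D-5L, stating the assumed correlation. At 0.5, power is still 82.6% with 30% loss. Adjustment for confounders related to modality may take back some of this gain, so the statement should mention it.

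The cost is one reworded paragraph. Under the first option the stated power becomes slightly less favourable; under the second the claim rests on a correlation that has to be justified.

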## Discussion

Dialysis has a great impact on the HRQoL of ESRD patients and dialysis is a very expensive treatment. More than 80% of Dutch dialysis patients are treated with ICHD although home dialysis could result in a better HRQoL and could be more cost effective. Therefore, we initiated the DOMESTICO study, which will investigate the effects of home dialysis on HRQoL in relation to clinical outcomes and costs, in comparison with ICHD. This nationwide cohort study will include 1600 incident dialysis patients over a period of 3 years. At time of submission of this manuscript, 338 patients have been included.

Although a randomised controlled trial (RCT) would yield the ultimate answer to our research question, this is not in accordance with the concept of shared decision making. A patient’s choice between home dialysis and ICHD is considered too fundamental, to let it be determined by chance. Indeed, an RCT in the Netherlands comparing PD with ICHD conducted in the past, stopped early due to poor patient recruitment; only 38 patients consented to be randomly assigned to either PD or ICHD [64]. Hence, DOMESTICO is designed as a prospective, observational cohort study collecting extensive parameters to correct for confounding by indication.

The results of this study will be of great importance for future ESRD patients when choosing a treatment, as HRQoL is increasingly acknowledged by clinicians and patients as an important aspect in the decision-making process. In addition, the results with respect to clinical outcomes will ameliorate the shared decision-making process. Finally, the data could give more guidance to healthcare professionals, in particular to assess which type of patients may benefit most from home dialysis.

## Data Availability

Not applicable.

## Abbreviations

CCMO: Central Committee on Research Involving Human Subjects
CRF: Case report forms
DOMESTICO: Dutch nOcturnal and hoME dialysis Study To Improve Clinical Outcomes
DSI: Dialysis Symptom Index
EQ5D-5L: EuroQol-5D-5L
ESRD: End Stage Renal Disease
HHD: Home haemodialysis
HRQoL: Health-related quality of life
ICHD: In-centre haemodialysis
iMCQ: iMTA Medical Cost Questionnaire
iMTA: Institute for Medical Technology Assessment
iPCQ: iMTA Productivity Cost Questionnaire
MCS: Mental Component Summary
PCS: Physical Component Summary
PD: Peritoneal dialysis
PRO: Patient Reported Outcome
PROM: Patient Reported Outcome Measure
QALY: Quality adjusted life year
RCT: Randomised controlled trial
RRT: Renal replacement therapy
SeMaS: Self-management screening questionnaire
SF: Short Form
